## Abstract

**Background:**

Aortic valve stenosis is one of the most common heart diseases in older patients. Nowadays, surgical aortic valve replacement is the ‘gold standard’ treatment for this pathology and the most implanted prostheses are biological ones. The three most implanted bovine bioprostheses are the Trifecta valve (St. Jude Medical, Minneapolis, MN, USA), the Mitroflow valve (Sorin Group, Saluggia, Italy), and the Carpentier-Edwards Magna Ease valve (Edwards Lifesciences, Irvine, CA, USA). We propose a randomized trial to objectively assess the hemodynamic performances of these bioprostheses.

**Methods and design:**

First, we will measure the aortic annulus diameter using CT-scan, echocardiography and by direct sizing in the operating room after native aortic valve resection. The accuracy of information, in terms of size and spatial dimensions of each bioprosthesis provided by manufacturers, will be checked. Their hemodynamic performances will be assessed postoperatively at the seventh day and the sixth month after surgery.

**Discussion:**

This prospective controlled randomized trial aims to verify and compare the hemodynamic performances and the sizing of these three bioprostheses. The data obtained may help surgeons to choose the best suitable bioprosthesis according to each patient’s morphological characteristics.

**Trial registration:**

ClinicalTrials.gov Identifier: NCT01522352

## Background

A critical aspect of aortic valve replacement is to achieve an optimal matching between the patient’s morphology and the implanted valve prosthesis. Specifically, the implanted prosthesis should not impair left ventricle ejection and this is even more crucial in cases where there is a small aortic annulus.

Pericardial bioprostheses have good hemodynamic performance because of their central opening and the flexibility of their leaflets. We already know that the durability of these pericardial bioprostheses is about 10 to 15 years [1,2].

At present, porcine bioprostheses are less well-performing than bovine pericardial ones [3] and among these, we focused on three bioprostheses offering high hemodynamic performance, especially for small aortic valves.

Since March 2010, a new pericardial aortic valve bioprosthesis (Trifecta valve, St. Jude Medical, Minneapolis, MN, USA) has been approved by the Food and Drugs Administration (FDA approval: St Jude Medical Trifecta Valve - P100029) and has recently received the CE mark. However, its hemodynamic characteristics still need to be compared with other bioprostheses already available on the market. Another bioprosthesis chosen for this trial is the Mitroflow valve (Sorin Group, Saluggia, Italy) [4]: it received the CE mark in July 2011 and it is characterized by an innovative phospholipid reduction treatment (PRT) expressively conceived to reduce the calcification process and, as a consequence, to improve its durability.

The third bioprosthesis is the Carpentier-Edwards Magna Ease valve (Edwards Lifesciences, Irvine, CA, USA) which has been designed by developing the renowned and highly performing Carpentier-Edwards PERIMOUNT valves. It allows easier implantation and its pericardial tissue is additionally treated to prevent calcification. This bioprosthesis received the CE mark in 2007 and FDA approval in 2009.

### Objectives of the Trivalve study

Each aortic valve has its own hemodynamic characteristics related to its geometry and each patient has their own morphology (weight, size, anatomy of aortic valve), as well as different physiological and pathophysiological conditions (ejection fraction, size and degree of calcification of the aortic annulus, degree of left ventricular hypertrophy and so on). Consequently, the choice of valve prosthesis and the surgical implantation technique are the only two directly adjustable variables; nonetheless, current literature does not provide clear differences among available bioprostheses.

The main objective of this study is to measure the hemodynamic performance of the three aortic bioprostheses: the Trifecta valve (St. Jude Medical, Minneapolis, MN, USA), the Mitroflow valve (Sorin Group, Saluggia, Italy), and the Magna Ease valve (Edwards Lifesciences, Irvine, CA, USA) Table 1.

**Table 1 T1:** Bioprosthesis characteristics

**Bioprosthesis type**	**Manufacturer**	**Valve diameters (mm)**
Trifecta	St. Jude Medical, Minneapolis, USA	19 to 29
Mitroflow	Sorin Group, Saluggia, Italy	19 to 29
Carpentier-Edwards Magna Ease	Edwards Lifesciences, Irvine, USA	19 to 29

Secondary end points will focus on 1) comparison between the effective aortic orifice area measured by computerized tomography (CT)-scan and echocardiography and the intraoperative measurement performed by a flat-head candle; 2) comparison between the diameter of the aortic orifice measured by a flat-head candle and the size of the implanted bioprosthesis provided by the manufacturer; 3) testing the accuracy of information provided by the manufacturers about bioprosthesis diameters.

## Methods and design

The Trivalve trial is a single-center, prospective, randomized trial. It will evaluate the short-term (six month) hemodynamic performance of three pericardial bioprostheses: the Trifecta valve (St. Jude Medical, Minneapolis, MN, USA), the Mitroflow valve (Sorin Group, Saluggia, Italy), and the Carpentier-Edwards Magna Ease valve (Edwards Lifesciences, Irvine, CA, USA), Figure 1.

**Figure 1 F1:**
[figure not shown]
Study’s flowchart.

ClinicalTrials.gov Identifier: NCT01522352.

### Patient’s enrollment and randomization

All patients scheduled for surgical aortic valve replacement by bioprosthesis will be screened according to inclusion and exclusion criteria (Table 2).

**Table 2 T2:** Inclusion and exclusion criteria

	
**Inclusion criteria**	Isolated aortic valve replacement or associated with myocardial revascularization and/or tricuspid valve repair
	Age (> 18 years and < 85 years)
**Exclusion criteria**	Emergency surgery
	Surgery other than full sternotomy
	Heart transplantation
	Any procedure involving the aorta (such as Bentall procedure, surgery for dissection, and so on)
	Redo surgery
	Active infective endocarditis
	Associated mitral valve surgery
	Heart failure (ejection fraction < 40%) or preoperative cardiogenic shock
	Systolic pulmonary arterial pressure > 60 mmHg
	Patient’s protocol refusal
	Pregnancy
	Mentally handicapped patients, pre-existing psychiatric disease or addiction
	Advanced respiratory failure (forced expiratory volume in 1 second or vital capacity below 50% of the predicted)
	Severe renal failure
	History of allergy or intolerance to iodinated contrast infusion
	Patients living more than 100 km away from the investigation center

Patients who have given their signed informed consent to participate in this clinical trial will undergo, preoperatively, a CT-scan and a transthoracic echocardiogram to measure the aortic annulus. Included patients will be randomly allocated to receive one of the three bioprostheses, in a 1:1:1 ratio. When a patient is considered eligible and informed consent has been obtained, randomization will be performed automatically (using STATA software (StataCorp, College Station, TX, USA) before surgery by an independent biostatistician. No stratification will be done. The selected bioprosthesis will be implanted.

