### Statistical considerations

#### Sample size estimation

The estimation of the number of patients required was considered by using previous data provided by the manufacturers on patients who had cardiovascular surgery which showed the mean postoperative gradients (mmHg) for the three studied types of valve (data not published). A minimum difference (δ) of 4 mmHg could be expected between the three types of valve for the most relevant diameters (21 and 23 mm). As the information concerning statistical variability was not provided in this document, the standard deviation (σ) was estimated on the basis of data from 103 patients observed in our center (84 with the Edwards Ease prosthesis, 19 with a Mitroflow diameter of 21 or 23 mm): σ = 5.8. Thus, for a type 1 error α = 0.05 (two-sided), a 90 %-power, δ = 4 and σ = 5.8, 44 subjects per group are needed. Taking into account multiple comparisons between the three randomized groups, 55 patients per group will be included (165 patients in total).

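### Annulus size is measured preoperatively and treated as crucial, yet neither the allocation nor the primary comparison uses it; pre-specify CT annulus diameter as a covariate in the primary model

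*Protocol article*

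**What the plan says.** On allocation, the section on enrollment and randomization states: "Included patients will be randomly allocated to receive one of the three bioprostheses, in a 1:1:1 ratio". It adds: "No stratification will be done". The same section says that consenting patients "will undergo, preoperatively, a CT-scan and a transthoracic echocardiogram to measure the aortic annulus", and Table 3 lists the CT native annulus diameter in millimetres as preoperative data.

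On the importance of annulus size, the Background says of ejection past the implanted valve that "this is even more crucial in cases where there is a small aortic annulus". The abstract hopes the data will "help surgeons to choose the best suitable bioprosthesis according to each patient’s morphological characteristics". The sample size section ties the planning difference to size as well: "A minimum difference (δ) of 4 mmHg could be expected between the three types of valve for the most relevant diameters (21 and 23 mm").

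On analysis, the Statistical analyses section compares six-month gradients by ANOVA with Tukey-Kramer, or by Kruskal-Wallis with Dunn's test if the ANOVA conditions fail. Comparisons are made first without adjustment and then, when appropriate, by linear regression on factors that may be unbalanced despite randomisation. Annulus size is not named among them. The section's one mention of ANCOVA follows the sentence on agreement between the sizing methods; it does not concern the primary endpoint.

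**The concern.** The protocol treats annulus size as a main patient-side determinant of how a valve performs, collects it before surgery, and then leaves it out of both the allocation and the primary test. Two things are at stake.

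- **Precision.** If annulus diameter predicts the six-month gradient, leaving it out keeps explainable variance in the error term. The comparison then has less power than the same 165 patients could give.
- **Chance imbalance.** With 55 per arm, one valve can by luck receive visibly more small annuli. The plan's answer is to choose adjustment factors after seeing how they fell. That makes the choice depend on the data. It also uses the wrong criterion, because a covariate is worth including for its relation to the outcome, whether or not it happens to be unbalanced.

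**Working it through.** **Inputs from the protocol.** δ = 4 mmHg, σ = 5.8 mmHg, two-sided α = 0.05, power 90%, 44 per group before and 55 per group after the allowance for multiple comparisons (165 in total).

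**Inputs not in the protocol, assumed.** Share of small annuli p = 20% to 50%, with 30% as the main case. Extra gradient with a small annulus g = 2 to 6 mmHg. Share of gradient variance explained by annulus R² = 10 to 20%.

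**1. The plan's own figure.** n = 2[σ(z₀.₉₇₅ + z₀.₉₀)/δ]² = 2[5.8 × (1.960 + 1.282)/4]² = 44.18. The stated 44 reproduces (45 if rounded up).

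**2. Precision at 55 per arm.** The standard error of a pairwise difference is 5.8 × √(2/55) = 1.11 mmHg. Using α = 0.05/3 to stand in for the three pairwise comparisons, power is 88.9% by the normal approximation and 88.0% by the t-test.

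**3. Chance imbalance.** Three independent binomial draws of 55 were simulated (200,000 to 400,000 trials). The gap is the highest minus the lowest share of small annuli among the three arms.

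| p | mean largest gap | gap ≥ 15 points | gap ≥ 20 points |
|---|---|---|---|
| 20% | 9.1 points | 10% | 3% |
| 30% | 10.4 points | 18% | 7% |
| 40% | 11.1 points | 22% | 10% |
| 50% | 11.4 points | 24% | 11% |

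**4. What that does to a contrast.** For a given pair of arms at p = 30%, the absolute gap has a median of 3/55 = 5.5 points and a 90th percentile of 8/55 = 14.5 points. Shift = g × gap:

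- g = 2: median 0.11, 90th percentile 0.29 mmHg
- g = 5: median 0.27, 90th percentile 0.73 mmHg
- g = 6: median 0.33, 90th percentile 0.87 mmHg

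The largest of the three gaps is naturally bigger: at g = 5 its shift has a median of 0.45 and a 90th percentile of 0.91 mmHg. All of these lie below the standard error of 1.11 mmHg, which already includes this source of variation.

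**5. Type I error.** In 20,000 simulated unadjusted ANOVAs per scenario with unstratified allocation and 30% small annuli, the rejection rate under the null was 0.050 for both g = 4 and g = 6.

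**6. Gain from adjustment.** The residual SD is 5.8 × √(1 − R²).

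- R² = 10%: SD 5.50, power at α = 0.05/3 of 92.2% (normal) or 91.4% (t-test)
- R² = 20%: SD 5.19, power of 95.0% (normal) or 94.5% (t-test)

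**7. Do the assumptions agree?** A two-class effect g with p = 0.3 explains g² × 0.3 × 0.7/5.8² of the variance. That is 2.5% at g = 2, 10% at g = 4 and 22% at g = 6. The R² range of 10 to 20% therefore belongs to the upper half of the range for g. At g = 2 the power gain would be about a point or less.

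**The case against.** The strongest reply is that nothing here is an error. Simple randomisation is valid and openly stated, the type I error is intact, and the plan already adjusts for factors that come out unbalanced. The main objective and primary endpoint compare the valves overall, and a separate analysis plan might name the covariates.

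Most of this stands, and it limits the point to efficiency. It does not remove the point, because the stated rule makes adjustment secondary and dependent on observed imbalance, and so forgoes the precision gain whenever the arms look balanced.

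A reader might infer more than the protocol supports:

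- **That the absence of stratification biases the comparison.** It does not. Random imbalance is part of ordinary sampling error, as the simulated type I error shows.
- **That one arm may have too few small-annulus patients for the comparison surgeons need.** The protocol plans no small-annulus subgroup comparison. Its Discussion links the choice of valve to the sizing objective.
- **That the CT value is always on file before allocation.** The text places imaging before surgery and says "When a patient is considered eligible and informed consent has been obtained, randomization will be performed automatically". The order of presentation suggests imaging first, and the limits on ejection fraction and pulmonary pressure suggest that an echocardiogram comes before eligibility. Nothing states outright that CT precedes allocation, and the flowchart is not shown.

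**Conclusion.** The point holds as a matter of efficiency and pre-specification. A baseline measurement that the protocol itself calls crucial is left out of the primary comparison and may enter only through a data-dependent rule. Validity is not affected. Chance imbalance would typically move a pairwise contrast by 0.1 to 0.3 mmHg, and by 0.3 to 0.9 mmHg at the 90th percentile, against δ = 4. The power available from adjustment is about 3 to 6 percentage points if annulus explains 10 to 20% of the variance, and little if it explains much less. These sizes rest on an assumed share of small annuli, annulus effect and R², none of which the protocol reports. The protocol does not support the conclusion that allocation must be stratified.

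**What to change.** In the Statistical analyses section, make the primary comparison a linear model (ANCOVA) of six-month mean gradient on valve group and preoperative CT annulus diameter. Enter the diameter as a continuous variable, pre-specified for all 165 patients, with Tukey-Kramer adjusted pairwise contrasts. Drop the selection of covariates by observed imbalance, and keep the unadjusted ANOVA as a supporting analysis. The covariate should be the preoperative CT value and not the implanted valve size, because the latter depends on the allocated valve. A preoperative annulus cannot be changed by the valve, so the model works whether CT came before or after allocation.

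The cost is one extra model term, a stated rule for a missing CT value, and a short amendment made before outcomes are compared. No patients or procedures are added.

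Stratifying the remaining allocations by CT annulus class is optional. Recruitment has run since March 2012, so it would cover only part of the sample. It would also require the CT value to reach the biostatistician before each allocation, and a cut-off fixed in advance.

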### Preoperative measurements

Preoperative CT-scan measured data, echocardiography and surgical measurements are shown in Table 3.

**Table 3 T3:** CT-scan, echocardiographic and surgical measurements

	**Preoperative data**	**Operative data**	**Day 7 data**	**Month 6 data**
CT-scan				
Native aortic annulus (mm)	X			
Ascending aorta diameter (mm)	X			
Echocardiography				
LVTS (mm)	X		X	X
LVTD (mm)	X		X	X
LVPWT (mm)	X		X	X
IVST (mm)	X		X	X
LVSF (%)	X		X	X
LVEF (%)	X		X	X
Pulmonary arterial pressure	X		X	X
Cardiac output (L/min^-1^)	X		X	X
Cardiac index (L/min^-1^/m^-2^)	X		X	X
Mean transvalvular gradient (mmHg)	X		X	X
Maximal transvalvular gradient (mmHg)	X		X	X
Aortic orifice area (m^2^)	X		X	X
Aortic regurgitation degree (0–4)	X		X	X
Paravalvular leak			X	X
Surgery				
Internal aortic annulus diameter (mm)		X		
Estimated valve diameter (mm)		X		
Implanted valve diameter (mm)		X		

IVST: inter ventricular septum thickness, LVEF: left ventricular ejection fraction, LVPWT: left ventricle posterior wall thickness, LVSF: left ventricular shortening fraction, LVTD: left ventricle tele diastolic diameter, LVTS: left ventricle tele systolic diameter.

### Surgery

During surgery, the aortic valve of the patient will be completely removed and the aortic annulus measured using a flat-head candle. This universal candle has been specifically designed to give a single objective value of the internal diameter of the aortic annulus. The Hegar dilators will not be used as its round shape and arched aerodynamics overestimate the size of the annulus by applying opening force to its passage (Figure 2). All measurements, early postoperative complications and reoperations for bleeding will be recorded in the operative report and in the case-report form.

**Figure 2 F2:**
[figure not shown]
Importance of the use of flat-head candles to measure the aortic ring (bottom of the picture) compared to Hegar dilators.

### Postoperative endpoints

All preoperative echocardiography collected measures will be reassessed at day seven and month six after surgery in addition to maximal and mean transvalvular gradients (mmHg). ICU, total hospital stay and any other postoperative complications will be recorded in the postoperative report and in the case-report form.

The primary endpoint is the mean transvalvular gradient (mmHg) six months after surgery. All secondary endpoints are indicated in Table 4.

**Table 4 T4:** Primary and secondary endpoints

	
**Primary endpoint**	Mean transvalvular gradient (mmHg), six months after surgery
**Secondary endpoints**	Effective aortic orifice diameter measured by CT-scan and echocardiography compared with the surgical data (mm)
	Mean transvalvular gradient (mmHg), at day seven after surgery
	Aortic bioprosthesis orifice area (m^2^), six months after surgery
	Diameter of the aortic orifice measured by a flat-head candle compared with the size of the implanted bioprosthesis (mm)

### Statistical considerations

#### Sample size estimation

The estimation of the number of patients required was considered by using previous data provided by the manufacturers on patients who had cardiovascular surgery which showed the mean postoperative gradients (mmHg) for the three studied types of valve (data not published). A minimum difference (δ) of 4 mmHg could be expected between the three types of valve for the most relevant diameters (21 and 23 mm). As the information concerning statistical variability was not provided in this document, the standard deviation (σ) was estimated on the basis of data from 103 patients observed in our center (84 with the Edwards Ease prosthesis, 19 with a Mitroflow diameter of 21 or 23 mm): σ = 5.8. Thus, for a type 1 error α = 0.05 (two-sided), a 90 %-power, δ = 4 and σ = 5.8, 44 subjects per group are needed. Taking into account multiple comparisons between the three randomized groups, 55 patients per group will be included (165 patients in total).

### Statistical analyses

All analyses will be performed using STATA v11 (StataCorp, College Station, TX, USA). A two-tailed *P*-value of 0.05 will be considered statistically significant. All analyses will be performed on an intention-to-treat (ITT) basis. The number of included patients and the rate of inclusions will be presented over time for each group. The patients will be described and compared between groups at baseline according to the following variables: compliance with eligibility criteria, epidemiological features, clinical features (including echocardiographic) and biological characteristics. The comparison concerning the postoperative means of the transvalvular gradients (measured by echocardiography at six months post surgery) between the three groups will be evaluated using ANOVA followed by the Tukey-Kramer *post hoc* test, or the Kruskal-Wallis nonparametric test if conditions of ANOVA are not met (homoscedasticity studied by Bartlett’s test and normality verify by Shapiro-Wilk) followed by Dunn’s test as appropriate. Comparisons between the groups will be realized systematically 1) without adjustment and 2) when appropriate, after adjustment (by multivariate linear regression model) on factors whose distribution could be unbalanced between the arms despite randomization. Quantitative secondary endpoints (for example hemodynamic data, CT-scan, in-hospital stay) will be analyzed as described above. Categorical parameters (that is, proportion of reoperations) will be compared between the groups using the chi-squared test or Fisher’s exact test, when necessary. To assess the relationships between the quantitative parameters (comparison between aortic orifice measurements by echocardiography, CT-scans, intraoperative measurement using the flat- candle versus the size of implanted valve prosthesis given by the manufacturer), the correlation coefficients (Pearson or Spearman), the Lin concordance coefficient and the intra-class coefficient (ICC) will be calculated. Later on, an ANCOVA could be proposed to consider group effect. The intra-group comparisons related to the quantitative criteria (hemodynamic data by echocardiography on preoperative period and at six months) will be made using paired the ANOVA or Wilcoxon test. Finally, to avoid bias induced by the presence of missing data, particularly with regards to the mean postoperative transvalvular gradient at six months (lost at follow-up or deaths), the primary analysis (ITT with imputation data determined according to quantity and type of missing data) will be completed on a second time by a per-protocol analysis.

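### When six-month gradients are both skewed and unequally spread, the plan's switch from ANOVA to Kruskal-Wallis no longer tests the mean gradients and can reject too often or lose power

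*Protocol article*

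**What the plan says.** - **Endpoint** (Postoperative endpoints): "The primary endpoint is the mean transvalvular gradient (mmHg) six months after surgery".
- **Target and default test** (Statistical analyses): "The comparison concerning the postoperative means of the transvalvular gradients" between the three groups "will be evaluated using ANOVA followed by the Tukey-Kramer" post hoc test.
- **Fallback** (same section): "or the Kruskal-Wallis nonparametric test if conditions of ANOVA are not met", followed by Dunn's test. Bartlett's test judges equality of variances, with "normality verify by Shapiro-Wilk". No level is given for these checks beyond the general rule that a two-tailed "value of 0.05 will be considered statistically significant". No unequal-variance test of means is named.
- **Adjusted analysis** (same section): a linear regression model, used when appropriate, alongside the unadjusted comparison.
- **Sample size** (Sample size estimation): "a 90 %-power, δ = 4 and σ = 5.8, 44 subjects per group are needed", raised to 55 per group for multiple comparisons. The single SD comes from 103 local patients, 84 with one valve and 19 with a second. None had the third.

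**The concern.** The stated target and the sample size both concern a difference in means in mmHg. Once either check rejects, the primary comparison becomes a rank test. Kruskal-Wallis and Dunn ask whether values in one arm tend to exceed those in another. That matches a comparison of means only if the arms share shape and spread, and a Bartlett rejection says the spread is not shared. Unequal variance alone is enough to trigger the switch, so the rank test serves as the remedy for a problem it does not solve.

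Two errors are possible. A valve may be declared different in mean gradient when the means are equal and only the spread differs, or a real 4 mmHg difference may be missed. In addition, after a switch the unadjusted test is on ranks while the adjusted model is still on means, so the two results answer different questions.

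Equal spread cannot be taken for granted, because the SD was estimated without any patient on the third valve.

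**Working it through.** **1. The plan's own figure.** For a pairwise difference in means, n per group = 2(z₀.₉₇₅ + z₀.₉₀)²σ²/δ² = 2 × (1.960 + 1.282)² × 5.8²/4² = 2 × 10.51 × 2.1025 ≈ 44.2. The stated 44 is reproduced (45 if rounded up; exact t power at 44 is 89.2%). For the step to 55, the same calculation gives 53 at α = 0.05/2 and 57 at 0.05/3. The sample size is not at fault, and it is built on means.

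**2. Why skew and spread matter together.** A lognormal variable has median = mean/√(1 + CV²). With an assumed mean of 12 mmHg:
- SD 4: 12/√(1 + 0.111) = 11.4
- SD 8: 12/√(1 + 0.444) = 10.0

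The means are identical, yet the medians are 1.4 mmHg apart, and a rank test responds to that. With symmetric data the medians would coincide.

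**3. Simulation of the rule under equal means.**
- *From the article:* 55 per arm, α = 0.05, SDs centred on 5.8.
- *Assumed, because the article does not give them:* mean gradient 12 mmHg (varied from 10 to 20), per-arm SDs, and a normal, gamma or lognormal shape. Also assumed: pre-tests at 5%, Shapiro-Wilk on pooled residuals, and complete data.
- *Rule:* Kruskal-Wallis if either pre-test rejects, otherwise ANOVA.
- *Runs:* 6,000 or 8,000 per cell. The standard error is about 0.2–0.3 points near 5% and about 0.5 points near 30%.

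Rejection rate in % under equal means of 12, plan's rule / Welch ANOVA:

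| SDs by arm | Normal | Gamma | Lognormal |
|---|---|---|---|
| 5.8/5.8/5.8 | 5.1 / 5.2 | 4.9 / 4.9 | 5.1 / 5.6 |
| 5/5.8/6.5 | 5.2 / 5.1 | 7.2 / 5.5 | 7.5 / 5.4 |
| 4/5.8/7 | 5.1 / 4.8 | 10.8 / 5.4 | 14.5 / 5.1 |
| 4/5.8/7.5 | 5.8 / 5.3 | 12.2 / 5.0 | 18.3 / 5.2 |
| 4/4/8 | 5.8 / 5.2 | 19.0 / 5.4 | 26.4 / 5.3 |
| 3/5.8/8 | 6.0 / 4.9 | 21.5 / 5.8 | 32.2 / 6.2 |

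Plain ANOVA without any switch rejects in 5.0–6.5% across these cells. With near-equal arms, ignoring the unequal variances does less harm than the planned remedy.

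**4. Dependence on the assumed mean (gamma).** A higher mean at the same SD means less skew.
- SDs 4/5.8/7: 13.4% at mean 10, 8.7% at 15, 7.7% at 20.
- SDs 4/5.8/7.5: 9.8% at mean 15, 8.2% at 20.
- SDs 5/5.8/6.5: 7.2% at mean 10, 6.6% at 15, 5.2% at 20.

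**5. How often the rule switches with equal SDs of 5.8.** Normal data: about 10% of trials (about 18% if Shapiro-Wilk is run per arm). Gamma data: 99.6% at mean 12, about 95% at 15, 76% at 20.

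**6. Power.**
- Gamma, means 12/12/16, SDs 4/5.8/9: plan's rule 66%, Welch 82%, plain ANOVA 88%.
- Equal SDs 5.8, means 12/12/16: plan 96.9% against Welch 96.6% (normal); 98.4% against 97.3% (gamma).
- Gamma, equal SDs 5.8, means 10/12/14: plan about 95%, Welch about 90%.

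**The case against.** The rule is written in advance, with both tests and both post hoc procedures named, so it leaves the analyst little discretion. With equal SDs it holds about 5% for every shape tried, and with skewed data and equal SDs the rank test is the more powerful choice. All of this stands.

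Several stronger readings are tempting, and the documents do not support them.

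- **Error is inflated whenever variances differ.** With normal data it stays at about 5–6% for every SD pattern tried. Skew and unequal spread are needed together.
- **The fallback will become the primary test.** Nothing in the article says that gradients are skewed. The switch rate runs from about 10% to nearly 100% depending on assumed shape and mean.
- **Pre-testing is itself the fault.** It contributes little; the harm comes mainly from the test switched to. Bartlett's sensitivity to non-normality adds little, because Shapiro-Wilk would usually trigger the same switch.
- **After a switch there is no mmHg estimate.** The planned regression could supply one, and reporting detail may properly sit in a fuller document.
- **Any rejection in these scenarios is false.** The distributions do differ. The rejection is wrong only as a statement about mean gradients, but that is the target the article names.

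**Conclusion.** The point holds as a conditional one. The article names mean gradients as its target and then fixes a rule that can replace the test of means with one that does not test them.

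If gradients are both skewed and unequally spread, the false-positive rate for equal means is about 5–8% for mild SD differences (5/5.8/6.5) and about 8–32% for larger ones, against about 4–6% for Welch ANOVA. If spread rises with the mean, power can fall, in one example from 82% to 66%. If gradients are close to normal, or the SDs are equal, the error rate is essentially nominal.

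That the rank test is the wrong remedy for unequal variance follows from the text and needs no simulation. The size of the effect is uncertain, because it rests on assumed means, shapes and per-arm SDs. The change is worth making before the data are analysed, since it costs little and the results are meant to guide the choice of valve.

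**What to change.** In Statistical analyses, remove the data-driven switch and name one primary analysis of the six-month mean gradient: Welch ANOVA with Games-Howell pairwise intervals, or a linear model on valve group with HC3 standard errors. Report the three pairwise mean differences in mmHg with simultaneous 95% confidence intervals. Keep Kruskal-Wallis with Dunn as a sensitivity analysis, described as a comparison of distributions. The adjusted linear model then addresses the same quantity as the unadjusted test.

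The cost is wording only, with no change to sample size or data collection. The statistical price arises if gradients are skewed with equal SDs: about 1 point of power with one arm 4 mmHg higher (98.4% to 97.3%), and about 5 points with means 10/12/14 (95% to 90%).

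### Adjustment covariates are chosen by observed baseline imbalance, and the primary ANOVA makes no use of preoperative annulus diameter; the cost is precision, not validity

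*Protocol article*

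**What the plan says.** All references are to the protocol article.

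- **Postoperative endpoints:** "The primary endpoint is the mean transvalvular gradient (mmHg) six months after surgery".
- **Statistical analyses:** this endpoint is compared between the three arms by ANOVA with Tukey-Kramer, or by Kruskal-Wallis with Dunn's test if normality or equal variance fails. Neither method carries a covariate. Comparisons are always made unadjusted and, when thought appropriate, again by linear regression adjusting "on factors whose distribution could be unbalanced between the arms despite randomization". The same section plans a between-arm comparison of baseline features.
- **Patient's enrollment and randomization:** "No stratification will be done". Consenting patients undergo, before surgery, "a CT-scan and a transthoracic echocardiogram to measure the aortic annulus". Table 3 lists the native annulus in mm as a preoperative CT measurement.
- **Background:** the prosthesis should not impair ejection, and "this is even more crucial in cases where there is a small aortic annulus". The objectives section names annulus size among the patient conditions that vary.
- **Sample size estimation:** the calculation uses an unadjusted SD and takes no credit for a covariate.

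The later remark in Statistical analyses that an ANCOVA might be proposed follows the agreement analyses of the measurement methods. It does not set a covariate for the primary comparison.

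**The concern.** In a randomised trial, baseline imbalance is due to chance. How unbalanced a factor looks says nothing about whether adjusting for it helps; that depends on how well it predicts the 6-month gradient. A rule keyed to imbalance can admit irrelevant factors and leave out prognostic ones.

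Two things follow. First, the adjusted comparison depends on a covariate choice made after the baseline data have been compared. A SAP that followed this rule faithfully would still choose covariates from the data. Second, the primary comparison ignores a measurement that the protocol already collects and regards as relevant. Without stratification, nothing in either the design or the primary analysis deals with a chance difference in annulus size between arms.

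**Working it through.** **Inputs from Sample size estimation.** Two-sided α = 0.05, 90% power, δ = 4 mmHg, σ = 5.8 mmHg; "a 90 %-power, δ = 4 and σ = 5.8, 44 subjects per group are needed", then "55 patients per group will be included (165 patients in total").

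**Input not in the documents.** The within-arm correlation r between preoperative annulus diameter and 6-month gradient. I show 0.1 to 0.5 as an assumption.

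**1. Reproduce the plan's figures.**
- n per arm = 2σ²(z₀.₉₇₅ + z₀.₉₀)²/δ² = 2 × 33.64 × (1.960 + 1.282)²/16 = 44.18, which agrees with the stated 44 (45 if rounded up).
- With α = 0.05/3 for three pairwise comparisons, n = 57, close to the stated 55.
- Both figures therefore rest on the unadjusted SD.

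**2. Power of the planned analysis at 55 per arm.** The standard error of a pairwise difference is 5.8 × √(2/55) = 1.106, so the noncentrality is 4/1.106 = 3.62. The Tukey critical value (studentized range for 3 groups and 162 df, divided by √2) is 2.365. Power from the noncentral t is 0.893.

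**3. Power with annulus diameter always in the model.** Residual SD = 5.8 × √(1 − r²), with 161 df.

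| r (assumed) | Residual SD | SE of difference | Tukey pairwise power |
|---|---|---|---|
| no covariate | 5.80 | 1.106 | 0.893 |
| 0.1 | 5.77 | 1.100 | 0.897 |
| 0.2 | 5.68 | 1.084 | 0.906 |
| 0.3 | 5.53 | 1.055 | 0.922 |
| 0.4 | 5.32 | 1.014 | 0.942 |
| 0.5 | 5.02 | 0.958 | 0.964 |

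**4. Effect of chance imbalance on the unadjusted estimate.** If two arms differ in mean annulus by one standard error of that difference, the unadjusted contrast shifts by r × 5.8 × √(2/55) = r × 1.106 mmHg. That is 0.33 mmHg at r = 0.3 and 0.55 mmHg at r = 0.5. An imbalance of two standard errors doubles these to 0.66 and 1.11 mmHg, against a δ of 4.

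**5. How an imbalance trigger behaves.** This used 20,000 simulated three-arm trials per scenario. The trigger was taken to be a baseline F-test at p < 0.05, a threshold that is assumed and not stated in the protocol.

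| Quantity | r = 0.3 | r = 0.5 |
|---|---|---|
| Type I error, unadjusted | 5.0% | 4.7% |
| Type I error, triggered rule | 4.9% | 4.1% |
| Unadjusted false rejection, only in trials with significant annulus imbalance | 8.0% | 16.9% |
| Omnibus power (one arm shifted by 4), unadjusted | 96.9% | 97.0% |
| Omnibus power, triggered rule | 97.0% | 97.3% |
| Omnibus power, always adjusted | 98.0% | 99.4% |

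Overall error is held in every case. The trigger recovers little of the gain that a fixed covariate offers.

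**The case against.** The strongest reply is that the primary inference is sound. The unadjusted ANOVA is fixed in the text, the trial is sized for its SD, its pairwise power is 0.893 against a 90% target, and its error rate is held. This stands, so the point concerns efficiency and pre-specification only. The raised false rejection rates in step 5 apply only to the few trials with marked imbalance, and there the plan does permit adjustment.

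Several stronger readings are tempting and are not supported:

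- **That annulus diameter is the main prognostic factor.** The objectives section lists it beside ejection fraction, calcification and hypertrophy without ranking them. The 21 and 23 mm in Sample size estimation are valve diameters, not CT annulus diameters. No correlation is given.
- **That annulus would normally be left out of the adjusted model.** A figure such as 5% of trials presumes a 5% baseline test. The protocol gives no threshold, and its wording also fits clinical judgement. A threshold and covariate list may sit in a SAP, so their absence is not the complaint.
- **That the plan produces two results of equal standing.** The unadjusted comparison is always made and the adjusted one is conditional. With the ANOVA sentence and the sample size, the natural reading is that the unadjusted result is primary.
- **That the CT measurement is wasted.** It serves a stated secondary endpoint.

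It is also fair to say that σ = 5.8 came at least partly from patients with 21 or 23 mm valves, so some variation due to size may already be out of it. Step 3 could then overstate the gain, although the trial's own SD might equally be larger.

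**Conclusion.** The point holds as one of efficiency and pre-specification. The protocol states a covariate rule that rests on the wrong criterion and is resolved only after the data are seen, and its primary comparison leaves a relevant, available baseline measurement unused.

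The gain in pairwise power is under one percentage point at r = 0.1, 1.3 points at r = 0.2, 2.9 at r = 0.3 and 7.1 at r = 0.5. All of it depends on an assumed correlation and on σ = 5.8 applying to the enrolled population. Nothing here shows bias over randomisation or an inflated type I error. The change is worth making because it is almost free and removes a choice that depends on the data.

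**What to change.** In Statistical analyses, replace both the ANOVA/Kruskal-Wallis sentence as it applies to the primary endpoint and the imbalance rule. Changing only the second would leave two candidate primary analyses. Suggested wording:

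> The primary analysis is a linear model of the 6-month mean transvalvular gradient on randomised valve and preoperative CT annulus diameter (continuous). The covariate is included whatever the observed balance between arms. Pairwise valve contrasts use a Tukey-type multiplicity adjustment. The unadjusted ANOVA with Tukey-Kramer, or Kruskal-Wallis with Dunn's test, is supportive.

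State also that the labelled size of the implanted valve is not a covariate. It is set after randomisation and can depend on the allocated valve's own sizing, so adjusting for it could remove part of the effect under study. The native annulus on preoperative CT cannot be altered by the valve implanted later.

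The cost is one degree of freedom (162 to 161) and a change of wording. No new measurement or patient is needed.
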